### Sample size

Determination of the sample size was guided by time constraints as well as by a thorough analysis of the patients' surgery rate conducted over a 1-year period at the recruitment site in accordance with our inclusion and exclusion criteria [20]. Furthermore, when one of the study goals is to obtain an estimate of variance in an outcome when an important difference between groups has already been identified (meaning that only the variance needs to be estimated), it is suggested that 10 to 20 participants per group is deemed sufficient to inform feasibility and to plan for a larger study [20].

### Randomization

Treatment allocation will be made based on randomization and minimization methods. Minimization criteria have been decided based on factors identified by the neurosurgeons known to delay postoperative recovery and include presence of diabetes, objective motor deficits in the lower limbs (confirmed by electromyography), self-reported severe disability (ODI score  $\geq 41$  %) and smoking habit. Patients will be randomized following a computer-generated list of random numbers. An independent research assistant blinded to patient assignment will sequentially number the envelopes containing intervention assignments according to the computer-generated randomization. Opaque and sealed envelopes will be opened in front of the participants at the end of the initial assessment visit.

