### Recruitment

Participants will be recruited at the *Centre de Santé et de Services Sociaux de Trois-Rivières* during their encounter with their treating neurosurgeon once the decision has been made to move forward with a surgical intervention. If deemed eligible, patients willing to participate in the study will be provided with an overview of the study purpose and content and they will be asked permission to be contacted by the research team. Further details will be given over the phone by a member of the research team and an assessment date will be set for the participant. Participants will be guided through the informed consent process and baseline demographics and physical measures will be collected. At the end of the initial assessment visit, a member of the research team will open the sealed envelope to randomly allocate participants to one of the two groups (intervention versus control). Treatments will be schedule after randomization for participants in the intervention group.

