### **Additional measurements**

Participants will complete a series of questionnaires and clinical examination procedures during the baseline assessment, allowing for exploratory analysis of any baseline features that might be predictors of intervention response. The questionnaires will include the following: demographics including age, gender, months lived with pain, presence of comorbidities and conservative interventions received so far. The Tampa Scale of Kinesiophobia will be used at every time assessment point to evaluate fear of movement and of re-injury because it has been found to be associated with poor performance on a number of physical tests and high scores have proven to be a powerful predictor of postoperative disability. The Beck Disability Index (BDI) will be used at every assessment time point as a screening tool for possible signs of high levels of anxiety and depression. The Minnesota Satisfaction Questionnaire (MSQ) will be used during the baseline

evaluation only in order to assess participant's satisfaction related to work conditions for those employed or on sick leave at the time of the study. Clinical examination will include weight and height measurements and a neurological exam of lower extremity deep tendon reflexes, assessment of fine touch and pinprick sensation, manual muscle testing for strength, ankle clonus and the Babinski test. In addition, participants from both groups will be asked about nature, length and frequency of any physical activities undertaken during the preoperative (assessed orally at the preoperative encounter) and postoperative periods (mailed questionnaire at 3-month and 6-month follow-up).

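### The protocol names minimization on four factors, but the list-and-envelope procedure it describes gives those factors no role, so balance on them is not ensured

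*Protocol*

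**What the plan says.** The Randomization section opens with the method: "Treatment allocation will be made based on randomization and minimization methods". It gives four criteria, chosen because the neurosurgeons regard them as delaying recovery: diabetes, motor deficit of the lower limbs, ODI of at least 41%, and smoking.

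The same section then gives the mechanics. "Patients will be randomized following a computer-generated list of random numbers". An independent research assistant is to "sequentially number the envelopes containing intervention assignments according to the computer-generated randomization". Finally, "Opaque and sealed envelopes will be opened in front of the participants at the end of the initial assessment visit".

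The Recruitment section agrees on the last step: "At the end of the initial assessment visit, a member of the research team will open the sealed envelope". Baseline measures are taken earlier in that same visit, and Table 1 places the ODI among the baseline questionnaires.

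The Statistical analysis section plans a repeated-measures ANOVA with Group, Time and their interaction. It names no covariate.

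**The concern.** Minimization sets each new assignment from two things: the new patient's factor levels, and how patients with those levels are already spread over the arms. Neither can be known when an assignment taken from a random list goes into a numbered envelope. The two halves of the section therefore describe different methods, and staff who follow the written steps would carry out only the second.

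Two things are at stake. First, four factors picked for their prognostic weight are left to chance in a 40-patient trial, and one of them is a threshold on a primary outcome. Second, the method named is not the method performed, which matters for a pilot meant to inform the design of a larger trial. An analysis plan cannot repair this, because allocation happens visit by visit.

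**Working it through.** **Step 1. The text.** The protocol gives no balance figure to reproduce, so the first check is a comparison of what minimization needs with what is described.

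| Minimization needs | Protocol describes |
|---|---|
| The new patient's four factor levels at the time of assignment | ODI collected at the visit; no step passes it, or the other factors, to whoever makes the assignment |
| Running totals by arm and factor level | None mentioned |
| An imbalance measure and an assignment probability | None; the stated source is a list of random numbers |
| An assignment made after the factors are known | An envelope that contains an assignment and is numbered in list order |

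Separate envelope sets for each factor combination would not rescue the wording. Four binary factors give 2^4 = 16 cells, and 40/16 = 2.5 patients per cell on average. That would also be stratification, not minimization.

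**Step 2. Illustration of size.** Inputs:
- N = 40 in two arms (Abstract). The ratio is not stated, so 1:1 is assumed.
- Four independent binary factors. Their prevalences are assumed, because the protocol gives none. ODI of at least 41% is held at 50%, and the other three are varied from 10–15% up to 50%.
- Measure: the largest between-arm difference in factor percentage over the four factors, counted if it is 20 points or more.
- Minimization rule: for each new patient, add up the arm differences at that patient's four factor levels with equal weights. Assign to the arm that reduces the sum with probability 0.8, or 0.5 if the sum is zero.
- 20,000 simulated trials per list setting and 6,000 per minimization setting.

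| Diabetes / motor / smoking / ODI | Simple list | 20/20 list | Minimization, 0.8 |
|---|---|---|---|
| 10 / 10 / 15 / 50% | 35% | 44% | 3% |
| 20 / 20 / 30 / 50% | 52% | 60% | 5% |
| 50 / 50 / 50 / 50% | 63% | 71% | 6% |

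Repeat runs differ by a point or so, hence 72% as the rounded upper end for the 20/20 list. For the ODI factor alone, the chance is about 22% (simple) or 27% (20/20), against 1–2% under minimization.

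**Step 3. Sensitivity to the cut-off.** With 20 per arm, 20 points is exactly 4 patients (4/20 = 0.20), so whether the boundary counts matters. In the middle row, strictly more than 20 points occurs in 36% of trials under the 20/20 list, 48% under the simple list and 3% under minimization. This lumpiness is why the 20/20 list looks worse than the simple list in the table. On a count measure (a difference of 4 or more patients), minimization gives about 11% in that row and the 20/20 list 60%. The gap is several-fold on every measure.

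**Step 4. Arm sizes.** If the list is unrestricted, a split of 25/15 or worse has probability 2 × P(X ≤ 15) with X ~ Binomial(40, 0.5), which is 0.154. The protocol does not say whether the list is restricted; with blocks this would not arise.

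**The case against.** **The wording leaves room.** The section speaks of methods in the plural and does not say when the envelopes are filled. The list might serve only the first patients or break ties. This is possible, but no such step is described, and the list is given as what patients are randomized by. It does rule out saying that minimization could not be done here. What stands is that the text does not provide for it.

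**A random list is valid.** This stands. List randomization leaves the treatment comparison unbiased in expectation, and chance imbalance costs precision. Baseline ODI and pain are measured, so an imbalance on them would be visible. A list may also balance the factors by luck. A reader might infer that the balance will fail or that the ODI and pain comparison is biased; the documents support neither.

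**It is a pilot.** Its main purpose is feasibility and estimation of effects. This also stands, and it lowers the urgency.

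**Two further inferences to avoid.**
- The motor-deficit factor is to be "objective motor deficits in the lower limbs (confirmed by electromyography"), while the baseline examination under Additional measurements lists "manual muscle testing for strength, ankle clonus and the Babinski test" and no electromyography. A reader might call this a contradiction. It is not one: patients come from the neurosurgeon's clinic, and the report may come from the clinical work-up.
- The assistant who numbers the envelopes is described as blinded. A reader might infer a concealment failure. The phrase can mean that the assistant does not know which patient receives which opaque envelope, and nothing shows otherwise.

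**Conclusion.** The concern holds as an inconsistency between the named method and the described one. Followed as written, the protocol allocates by list, and balance on diabetes, motor deficit, ODI and smoking is not ensured. That conclusion rests on the text alone.

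The size is illustrative: about 35–63% (simple list) or 44–72% (20/20 list) of trials with at least one factor 20 points or more apart, against about 3–6% under 0.8 biased-coin minimization. These figures assume 1:1 allocation, independent factors and prevalences that the protocol does not supply, and they shift with the cut-off. The consequence is lost precision and a misdescribed method, made somewhat worse because the planned ANOVA names no adjustment for the four factors. In a feasibility pilot this should be fixed, but it is not a reason to hold the trial.

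**What to change.** State one procedure that can be carried out.

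**Preferred.** Once baseline data are complete, the four factors go by phone or web to the independent research assistant already named. The assistant runs a minimization program with a random element (for example 0.8 to the favoured arm) and releases the assignment. The protocol should give the weights, the assignment probability and how concealment is kept. The analysis should then adjust for the four factors.

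**If envelopes are kept.** Delete the minimization claim and describe the blocked or stratified list actually used.

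**Cost.** Protocol wording and, for the first option, a short program; no extra patients. The small downside of the first option is that the assistant must be reachable at each of the 40 baseline visits.

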### Interventions

Patients will be randomly allocated to one of the two following groups: (1): an intervention group (preoperative supervised physical training) and (2) a control group (hospital standard preoperative management). The intervention group will be trained 3 times per week for 6 weeks prior to their surgery.

### Preoperative physical training

The preoperative physical training will be supervised by a chiropractor and a certified kinesiologist. Each 30-minute training session will aim to improve strength, muscular endurance and spinal stabilization and will be divided into 3 phases. The first phase consists of a 5-minute cardiovascular warm-up (stationary bicycle). The second consists of three exercises (squat, superman, legs raise) designed to increase stabilization of the spine achieved by co-contracting the abdominal and back muscles. The third phase involves two exercises (hips raise, hips abduction) to strengthen the thigh and hip muscles. The training protocol has been developed so that each specific exercise can be modified to obtain three different levels of difficulty in order to provide a safe and individualized training experience for each participant. Intensity and complexity of the exercises will be gradually increased throughout the sessions, depending on each participant's individual progress. Our choice of intervention was informed by a scoping literature review of the nature and effectiveness of currently used interventions for patients undergoing any type (excluding scoliosis) of low back surgery (work submitted for publication). Figure 1 illustrates a typical example of the possible modifications for the proposed exercises.

### Hospital preoperative management

Patients undergoing surgical intervention at the regional hospital do not receive any particular physical intervention (exercises, manual therapy, etc.). On their last encounter before the day of surgery they are given a

pamphlet summarizing tips on how to keep a good back posture when getting in or out of bed and when sitting down. All participants will be questioned on the amount and type of physical activity performed weekly, if any, regardless of their group allocation.

### Data collection

This study will take into consideration the evaluation of both clinical parameters (pain intensity, lumbar disability, use of pain medication, quality of life) and physical functional capacities (endurance and strength of lumbar region muscles, lumbar ranges of motion, walking abilities, cardiovascular capacity). All physical measures will be obtained during in-clinic assessments; at baseline, at the end of the training program (6 weeks after baseline evaluation for control participants), and at 6 weeks postoperatively and will provide insight into why the prehabilitation program was successful or not. In addition, self-reported questionnaires will be mailed at 3 and 6 months postoperatively in order to provide a subjective evaluation of patients' recovery at mid-term and long-term. The timeline illustrating the various interventions and outcome assessments is presented in Table 1.

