## Abstract

**Background:** Degenerative lumbar spinal stenosis is a prevalent condition in adults over the age of 65 and often leads to deconditioning. Although the benefits of surgery outweigh those of conservative approaches, physical rehabilitation may be used to improve function and to minimize the risk of persistent dysfunction. This study protocol was designed to establish the feasibility of a full-scale randomized controlled trial and to assess the efficacy of an active preoperative intervention program on the improvement of clinical parameters and functional physical capacity in patients undergoing surgery for lumbar spinal stenosis.

**Methods/Design:** Forty patients will be recruited and randomly allocated to one of the 2 treatment arms: 6 weeks supervised preoperative rehabilitation program (experimental group) or hospital standard preoperative management (control group). The intervention group will be trained three times per week, with each session aiming to improve strength, muscular endurance, spinal stabilization and cardiovascular fitness. Intensity and complexity of exercises will be gradually increased throughout the sessions, depending on each participant's individual progress. Primary outcomes are level of low back disability and level of pain. Secondary outcomes include the use of pain medication, quality of life, patient's global impression of change, lumbar extensor muscles endurance, maximum voluntary contraction of lumbar flexor and extensor muscles, maximum voluntary contraction of knee extensors, active lumbar ranges of motion, walking abilities, and cardiovascular capacity. Both the primary and secondary outcomes will be measured at baseline, at the end of the training program (6 weeks after baseline evaluation for control participants), and at 6 weeks, 3 and 6 months postoperatively.

**Discussion:** This study will inform the design of a future large-scale trial. Improvements of physical performances before undergoing lumbar surgery may limit functional limitations occurring after a surgical intervention. Results of this study will provide opportunity to efficiently improve spinal care and advance our knowledge of favorable preoperative strategies to optimize postoperative recovery.

**Trial registration:** US National Institutes of Health Clinical Trials registry NCT02258672, 10 February 2014.

**Keywords:** Prehabilitation, Exercise therapy, Lumbar spine, Spinal stenosis, Surgery

\* Correspondence: [contact]

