### **Statistical analysis**

Participants' characteristics will be summarized using descriptive statistics (mean, standard deviation). The equivalence of groups at baseline in terms of demographic and clinical variables will be assessed using independent samples *t* tests for continuous variables and chi-square tests for categorical variables. Following an intention-to-treat principle, estimates of efficacy (Group and Time main effect, as well as Group x Time interactions) will be analyzed using a repeated-measure analysis of variance (ANOVA). The statistical significance level will be set at 5 % and missing data will be analyzed using multiple imputation methods.

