### **Ethical considerations**

Considering that patients are on a waiting list for their surgical intervention, it is possible that the training period will vary from one individual to the next. No intervention presented herein will delay or interfere with the patients' surgical planning. All participants have the right to withdraw from the study at any time and the research team reserves the right to stop the trial if it is believed that there are risks of adverse events or if the patients' condition or symptoms worsen.

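### Follow-up after the preoperative visit is tied to surgery alone, so a randomized patient who is never operated on has no later assessment and by default gets imputed postoperative scores

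*Protocol*

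**What the plan says.** **Entry and randomization.** Patients are approached "once the decision has been made to move forward with a surgical intervention" (Protocol, Recruitment). Allocation comes at baseline: "At the end of the initial assessment visit, a member of the research team will open the sealed envelope to randomly allocate participants" (same section). Surgery still lies ahead and its date is not fixed: "Considering that patients are on a waiting list for their surgical intervention" (Ethical considerations).

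**Outcome times.** The Abstract, Data collection and Table 1 give five: baseline; a preoperative visit at the end of training, or six weeks after the baseline visit in controls; and 6 weeks, 3 months and 6 months after surgery. For the last two, "self-reported questionnaires will be mailed at 3 and 6 months postoperatively" (Data collection). No other starting point for follow-up appears.

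**Analysis.** "Following an intention-to-treat principle, estimates of efficacy" come from a repeated-measures ANOVA with group, time and their interaction, and "missing data will be analyzed using multiple imputation methods" (Statistical analysis). Nothing is said about a randomized patient whose operation never takes place.

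**The concern.** Surgery happens after randomization, and whether it happens may depend on the arm. The Background section itself cites weak evidence that exercise helps disability and pain in the short run, and notes that active physical therapy is advised as a first step in this condition. A patient who improves over six weeks of training may decide against surgery.

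Such a patient has a real ODI and a real pain score three and six months later, and both can be obtained by post. The schedule does not ask for them. Those scores then look missing, and the only stated remedy for missing data is imputation. What would be imputed is a score following an operation that the patient did not have. If non-operation is more frequent in one arm, the comparison mixes the effect of the programme with these constructed values.

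For a pilot meant to inform a larger trial, the number not operated on in each arm is also a result in its own right. Measures of feasibility does not list it separately.

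**Working it through.** The protocol has no power calculation or dropout figure to reproduce. Its only sample-size figure is 40, from "Forty patients will be recruited and randomly allocated to one of the 2 treatment arms" (Abstract). This agrees with the upper end of its rule of 10 to 20 per group (Sample size): 2 × 20 = 40.

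**Step 1: what one unoperated patient loses.**

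| ODI/NRS time point | Counted from | Exists without surgery? |
|---|---|---|
| Baseline | entry | yes |
| Preoperative | end of training, or baseline + 6 weeks | yes |
| 6 weeks | operation | no |
| 3 months | operation | no |
| 6 months | operation | no |

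The loss is 3/5 = 60% of that patient's time points, including all those after the preoperative visit.

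**Step 2: how much data could be affected.** There are 40 × 3 = 120 postoperative patient-visits and 40 × 5 = 200 in all. The protocol gives no rate of non-operation, so *c* is assumed.

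| Assumed *c* | Patients (40*c*) | Postoperative visits affected (of 120) | Share of all 200 | Share of one arm's postoperative data if all fall in that arm (40*c*/20) |
|---|---|---|---|---|
| 5% | 2 | 6 (5%) | 3% | 10% |
| 10% | 4 | 12 (10%) | 6% | 20% |
| 15% | 6 | 18 (15%) | 9% | 30% |
| 20% | 8 | 24 (20%) | 12% | 40% |

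The chance of at least one such patient among 40 is 1 − (1 − *c*)^40: 0.87 at 5% and 0.985 at 10%.

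**Step 3: what it could do to the contrast.** Let *g* be the true mean ODI of unoperated patients minus the mean that imputation gives them. The error in the group difference is (p_int − p_ctl) × *g*, where p_int and p_ctl are the proportions not operated on in the intervention and control arms. None of these inputs is in the protocol. Assume for illustration p_int 10–20%, p_ctl 0–5% and |*g*| of 8–15 ODI points:

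- smallest: (0.10 − 0.05) × 8 = 0.4 points
- largest: (0.20 − 0) × 15 = 3.0 points

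With an assumed SD of 15 to 18 and 20 per arm, the standard error of the difference is SD × √(2/20), or 4.7 to 5.7. The error is then 0.4/5.7 = 0.07 to 3.0/4.7 = 0.64 standard errors.

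The sign follows *g*. Higher ODI is worse, so if unoperated patients do worse than imputed (*g* > 0), the arm with more of them looks too good. If they stayed unoperated because they improved, *g* may be zero or negative, and that arm is unaffected or looks too bad.

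**The case against.** The strongest reply is that the protocol never says unoperated patients will be imputed. The imputation model and the handling of non-operation may sit in a statistical analysis plan that is not shown, and a model could use the patient's own baseline and preoperative scores. This stands as far as it goes: imputation is the default reading of an unqualified rule, not an explicit instruction. It does not answer the schedule problem. Which data are collected is protocol content, and no later analysis plan can recover questionnaires that were never sent.

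A second reply is that counting from surgery suits a trial about recovery after surgery, and that patients enter only once an operation has been decided. Both points are fair. They argue for keeping the surgical anchor for operated patients and may make non-operation uncommon. They do not say what happens to the remaining randomized patients under intention to treat.

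A reader might infer more than the documents support:

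- *That unoperated patients have no outcome data.* They still have the preoperative visit.
- *That deferred operations cause the same loss.* Deferred patients keep all three visits, only later, unless the trial closes first (Trial status expects completion by the end of 2015).
- *That the bias always favours the arm with more unoperated patients.* This requires them to do worse, which the example of patients who improve and decline surgery could reverse.
- *That cancellations will be hidden as attrition.* Attrition is a named feasibility measure and Table 1 records perioperative data, so who was operated on should be known. The gap is only that separate reporting is not promised.
- *That the analysis ceases to be intention to treat.* Keeping every patient in the assigned arm and imputing is a common form of it.

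**Conclusion.** The point holds in a limited form. For a randomized patient who is never operated on, the protocol schedules no assessment after the preoperative visit, and its stated rules lead by default to imputed scores after an operation that did not occur. The loss of 3 of 5 time points per such patient follows directly from the schedule.

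How many patients this concerns, and how far and in which direction the contrast would move, cannot be settled from the document. The range of 0.4 to 3.0 ODI points rests wholly on assumed rates, an assumed gap and an assumed SD, and its sign is open. The sample size is not affected. The point still deserves correction because uncollected scores cannot be recovered later and the remedy is cheap.

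**What to change.** 1. **Data collection:** state that patients not operated on are mailed the ODI and NRS at fixed times from randomization, chosen to match the expected timing of the 6-week, 3-month and 6-month visits. A fixed time from randomization is safer than a planned operation date, which a waiting-list patient may not have. For example, if surgery were expected right after the six-week programme, the first mailing would fall at 6 + 6 = 12 weeks; a longer usual wait would move it accordingly.
2. **Statistical analysis:** state that these observed scores are analysed in the assigned arm, and that multiple imputation is limited to outcomes that were requested but not returned.
3. **Measures of feasibility:** report the number not operated on, by arm, separately from attrition.

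The cost is about one sentence in each section and a few extra mailings. The downside is one of interpretation: the intention-to-treat estimate becomes the effect of offering prehabilitation whether or not surgery follows. An analysis of operated patients can be shown as supportive, with the caution that being operated on may itself depend on the arm.
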